### Interim analyses {21b}

There are no interim analyses planned. Given that both adjuvant therapy procedures after relief of a chronic subdural hematoma medication with TXA and embolization of the MMA are already validated in clinical practice and in the literature, there is no reason to anticipate exceptionally poor outcomes or unexpected complications. Furthermore, reaching a statistically significant difference between the groups before the planned end of the study is unlikely with the anticipated cohort size.

### Methods for additional analyses (e.g., subgroup analyses) {20b}

A subgroup analysis is not yet planned but will be added if necessary.

### Methods in analysis to handle protocol nonadherence and any statistical methods to handle missing data {20c}

Missing data will be avoided as much as possible by planning scheduled visits well in advance. If a significant amount of data is missing for any of the primary endpoints or other analyses, we will conduct exploratory analyses to assess the impact of the missing data, according to the EMA-guidelines [4]. Depending on the amount of missing data, it will be assessed whether missing covariates can be replaced by multiple imputation with predictive mean adjustment.

### Plans to give access to the full protocol, participant‐level data and statistical code {31c}

The trial was registered on 02 Feb 2024 (http://www.drks.de/DRKS00033515) with the German Clinical Trials Registry (Deutsches Register Klinischer Studien [DRKS]) as a primary registry of the WHO International Clinical Trials Registry Platform (ICTRP; https://trialsearch.who.int/). In addition, data sets.

analyzed in the current study and the statistical code are available upon reasonable request from the corresponding author, as is the full protocol.

## Oversight and monitoring

### Composition of the coordinating center and trial steering committee {5 d}

This study is conducted as a multicenter study. The coordinating team consists of the principal investigator and the study team, which includes the participating physicians from the leading center (Department of Neurosurgery at the Bundeswehrkrankenhaus Ulm), the physicians responsible for the study at each participating center, and the documentation assistants from the initiating center. This group meets regularly (once a quarter) to discuss the progress of the study and any problems that may arise, and to ensure compliance with the study protocol. They support the study on a day-to-day basis. The principal investigator works with the study team to solve any recruitment problems that may arise. In addition, the principal investigator ensures that new study staff receive appropriate training and instruction. Each co-principal investigator of a participating study center is thoroughly informed about the study protocol in a kick-off meeting before the start of study participation. In addition, meetings with all co-investigators will take place at regular intervals to discuss the progress of the study.

The steering committee of the study consists of the PI, experts from the participating departments of neurosurgery and neuroradiology, and the ethics committee of the coordinating center. Regular meetings of the steering committee are planned every 6 months.

### Composition of the data monitoring committee, its role and reporting structure {21a}

Safety of the trial participants will be ensured by an institutional panel consists of the ethical commission, two clinical experts who are independent of the trial and two members of the study team. They monitor serious adverse events (SAEs), the ethical conduct of this study, ensuring that the trial is implemented according to the protocol and that data are collected appropriately.

### Adverse event reporting and harms {22}

Adverse events are defined as any undesirable experience occurring to a subject during the study, whether or not considered related to the investigational product (TXA) or investigational intervention (embolization). After participants have provided consent and been enrolled in the study, adverse events or complications of the treatment, will be documented and recorded until the end of the study period. Any serious adverse event that occurs in this trial will be reported to the principal investigator (PI). The PI must decide whether the participant can continue to participate in the study or whether he or she has to be excluded. The study team in every participating center will take responsibility for the treatment of the trails related adverse events or complications. The PI of the study will consider the continuation or discontinuation of the research under the following circumstances:◦ If a serious adverse event or disease report suggests that continuing the study poses safety concerns◦ If recruiting participants for the study becomes challenging, making it difficult to achieve the planned number of cases◦ When significant new information regarding the quality, safety, or efficacy of the medication (TXA) and interventional procedure (embolization) is obtained

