### Criteria for discontinuing or modifying allocated interventions {11b}

Patients may withdraw their consent at any time without providing a reason and thus terminate their participation in the study prematurely. Withdrawal from the study and reasons, if known, will be documented. Study treatment stops if a surgical treatment for the CSDH is necessary during follow-up, in case of subsequent occurrence of an exclusion criterion or in occurrence of treatment-related complications during treatment. Crossover to the other study arm is not possible after the start of treatment in the respective study arm. Moreover, the principal investigator is entitled to terminate the study prematurely if new scientific findings in favor of one or the other treatment violate the equipoise principle.

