## Assignment of interventions: blinding

### Who will be blinded {17a}

Due to the study design, which compares a drug therapy with an interventional procedure, neither the patients nor the physicians can be blinded. In addition, the embolizate used in the embolization of the patients treated in the control group will always be visible in the imaging control examinations in both MRI and CT, so that neither the radiologist nor the neurosurgeon can be meaningfully blinded here.

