**Fig. 2 Fig2:**
[figure not shown]
Preoperative volume measurement of a right-sided hemispheric chronic subdural hematoma using the CT data set

The following intervention-associated complications will be documented as part of the study:Vascular dissections caused by the guidewireDislocation of embolized materialIschemia caused by vascular occlusion during the interventionInflammation or abscesses at the puncture siteVascular fistula in the area of the puncture siteRetinal blindnessEpidural hematomas after perforation of the meningeal arteryAllergic reactions to the contrast mediumAcute renal failure

The following complications or adverse events associated with the use of tranexamic acid will be documented:Intolerance reactionsPulmonary embolismsVenous thrombosisEpileptic seizuresMyocardial infarctionsCerebral ischemic infarctionsAcute renal failure

All research data, including baseline data (NIHSS, mRS, hematoma volume, patient demographics and characteristics) prior to surgery, will be collected anonymously in an electronic data collection form at each study center. The PI of the trial summarizes these for all centers and exports data for statistical analysis. All investigators will be trained to perform outcome measurements and will be introduced to the data management prior to recruitment of the first patient.

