### Confidentiality {27}

All persons involved in the study are bound to confidentiality. All data is collected and analyzed in pseudonymous form. Extensive measures are taken to protect the data, especially personal data, from access by third parties. Local therapy files and study data are kept in locked cabinets and are only accessible to the study staff and the respective treating therapists, who are subject to legal confidentiality.

All treatment cases are managed using identification codes or anonymized registration numbers. The semantics of the patient coding is specified by the Principal Investigator (PI) of the trial and consists of the study center number (two digits) and a consecutive number within the study center (three digits). The correspondence table of anonymization codes and names as well as the consent form with the names are kept strictly in a separate, lockable document storage and managed by the principal investigator of the respective center. The pseudonymous research data will only be shared after a data transfer agreement is signed. If participants withdraw their consent to the study, they will be asked about the reasons for their early withdrawal. The data collected to date will continue to be used and analyzed as part of the study unless the participants withdraw their consent to the processing of their data.

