## Statistical methods

### Statistical methods for primary and secondary outcomes {20a}

The baseline data and outcome parameters are subjected to a simple descriptive data analysis (median, minimum, maximum and standard deviation in each case; mean only for metrically scaled characteristics).

For difference tests for nominal variables (gender, use of anticoagulation prior to surgery, occurrence of complications due to adjuvant therapy procedures, need for revision surgery), the Pearson chi-squared test is used.

For difference tests of ordinally scaled measured variables (NIHSS, mRS) within the respective groups at different points in time (linked samples), the data collected is tested for normal distribution using the Shapiro–Wilk test. In the case of a parametric distribution, the *t*-test is used for linked samples. In the case of a non-parametric distribution, the Wilcoxon test is used for connected samples (for two-group tests).

For the bivariate dependency analysis of the ordinal scaled characteristics between the two groups at the same point in time, the *t*-test for unconnected samples is used for a parametric distribution and the Mann–Whitney *U*-test for a non-parametric distribution after applying the Shapiro–Wilk test.

For metric variables (hematoma volume), which are subject to a normal distribution, the *t*-test for dependent samples is used to analyze the respective groups at different points in time. In the case of a non-parametric distribution, the Wilcox sign-rank test is used for the analysis.

For the bivariate dependency analysis of the metric characteristics between the two groups at the same point in time, after applying the Shapiro–Wilk test, the *t*-test for unrelated samples is used for a parametric distribution and the Mann–Whitney *U*-test for a non-parametric distribution.

In addition, a logistic regression is tested with the revision rate as the dependent variable and the treatment groups and baseline data as independent variables.

Furthermore, a correlation analysis of the relationship between the postoperative volume size and the revision rate as well as the postoperative neurological assessment and the revision rate is performed, in each case for mixed scaling pairs with the chi-squared test. The respective singular correlation analysis is followed by an analysis of the existence of a partial correlation between the two parameters in relation to the revision rate.

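### After a serious adverse event the unblinded PI may end a randomised patient's participation in the study, whereas the discontinuation section only stops study treatment; outcome-related loss of follow-up can result

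*Protocol article*

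**What the plan says.** Two sections of the protocol article deal with what follows a serious event after randomisation.

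- **Adverse event reporting and harms {22}.** All SAEs, in either arm, are reported to the PI. Then: "The PI must decide whether the participant can continue to participate in the study or whether he or she has to be excluded". The section gives no criteria, names no independent assessor, and does not say whether an excluded patient is still followed.
- **Criteria for discontinuing or modifying allocated interventions {11b}.** "Study treatment stops if a surgical treatment for the CSDH is necessary during follow-up", and also "in case of subsequent occurrence of an exclusion criterion or in occurrence of treatment-related complications during treatment". The consequence here is the end of study treatment. The section does not say that participation or follow-up ends, nor that it continues.

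Four other statements bear on the point.

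- Who will be blinded {17a}: "neither the patients nor the physicians can be blinded".
- Data management {18a, 19}: "The PI of the trial summarizes these for all centers and exports data for statistical analysis".
- Statistical methods {20a}: the nominal variables compared by the Pearson chi-squared test include "occurrence of complications due to adjuvant therapy procedures, need for revision surgery".
- Confidentiality {27}, on patients who withdraw consent to the study: "The data collected to date will continue to be used and analyzed as part of the study unless the participants withdraw their consent". The consent meant at the end of that sentence is the one for data processing. No corresponding rule is given for a patient whom the PI excludes.

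**The concern.** Stopping a treatment and leaving a study are different things. A patient who stops the allocated treatment can still be scanned, examined and counted in the randomised arm. A patient who is excluded from the study ordinarily cannot.

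The trigger for exclusion arises after randomisation and overlaps with what the trial measures, because complications and revision surgery are both compared between arms. The person who decides knows the arm and also pools the data of all centers. The complications listed in the data collection section differ by arm: puncture-site and vessel injury, displaced embolic material and epidural hematoma for embolization; venous thrombosis, pulmonary embolism, seizures and infarction for tranexamic acid. Exclusions therefore cannot be assumed to balance.

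At stake are the hematoma volumes still to be measured up to 3 months, any later revision, and the 3-month mRS and NIHSS. Patients with a serious event are likely to differ from the rest on these measures, so the missing values would not be a random sample.

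**Working it through.** **1. The two rules side by side.** A treatment-related complication that is also serious falls under both sections. Under {11b} the study treatment stops. Under {22} the patient may be removed from the study. The article does not say which rule governs, or whether exclusion in {22} means from treatment or from follow-up. In the embolization arm the procedure is a single act and the only study intervention (adherence section {11c}). Once it has been done, little study treatment is left to stop, so exclusion there would act mainly on follow-up.

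**2. What would be lost and what would not.**
- The SAE that triggers the decision has already been reported, so it is on record.
- A revision is documented with its interval from the primary operation (Outcomes {12}, secondary outcome), so a revision before exclusion is on record too.
- Data due after the exclusion would not be collected: the remaining volumes, any later revision, and mRS and NIHSS at 3 months.

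**3. The plan's own sample size.** Inputs from Sample size {14}: recurrence 10% with embolization and 2% with tranexamic acid, α = 0.05, power above 0.8. Sidedness is not stated; two-sided is assumed here. The mean rate is 0.06. With pooled variance and no continuity correction:

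n = [1.960·√(2·0.06·0.94) + 0.842·√(0.10·0.90 + 0.02·0.98)]² / 0.08² = (0.6583 + 0.2786)² / 0.0064 = 137.2, rounded up to 138 per arm, 276 in total.

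The stated figure is reproduced, and power at 138 per arm is 0.802. No dropout allowance is stated. If 2%, 5% or 10% of each arm could not be analysed for revision, at random and equally in both arms (assumed), power would be 0.794, 0.782 or 0.759. This is loss of precision only, without bias.

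**4. Worst case for the revision rate.** The article does not describe this case. It assumes that recorded revisions in one arm are removed from both numerator and denominator.

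*At the planning rates.* 10% and 2% of 138 are about 14 and 3 patients. Pearson chi-squared without continuity correction, z = (p₁ − p₂) / √[p(1 − p)(1/n₁ + 1/n₂)], p being the pooled rate:
- 14/138 v 3/138: 10.1% v 2.2%, z = 0.0797/0.0289 = 2.75, p = 0.006.
- Five revised embolization patients dropped (assumed), 9/133 v 3/138: 6.8% v 2.2%, z = 0.0459/0.0250 = 1.84, p = 0.066.

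*With no true difference.* Suppose the true rate is 10% in both arms and a fraction x of the revised patients in one arm is dropped (assumed range). The observed rate there is 0.10(1 − x)/(1 − 0.10x). The rejection rate of the two-sided 5% test follows from the normal approximation:

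| x | Observed rate in that arm | Rejection rate |
|---|---|---|
| 20% | 0.080/0.98 = 8.2% | 8% |
| 30% | 0.070/0.97 = 7.2% | 13% |
| 50% | 0.050/0.95 = 5.3% | 31% |

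**5. The primary outcome.** Late volumes are the data most exposed to early exit. The article gives no standard deviation, expected difference or SAE rate, so no figure for the volume comparison can be derived from it.

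**The case against.** The strongest reply is that {22} permits exclusion but does not order it, and that it nowhere says recorded data are discarded. The same section has adverse events and complications recorded to the end of the study period. Revision and its timing are documented separately, and {11b} has its own, more specific rule for revision surgery. SAE is not defined in the article, so it is uncertain whether a revision counts as one. A panel that includes two independent clinical experts monitors SAEs and data collection {21a}. Finally, the definition of an analysis set may stand in the full protocol or in an analysis plan that is not shown.

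Most of this stands. A reader might infer from {22} that patients with an SAE are removed from the arm comparison together with their events, so that the type I error of the trial is 8% to 31%. The documents do not support that inference. A revision that is recorded and kept contributes to the revision rate whether or not the patient is later excluded. Nor is the lack of a named analysis set a fault in an article.

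The reply does not remove the conflict of wording. {22} speaks of participation in the study and {11b} of treatment. The rule that keeps data already collected is written for withdrawal of consent only. The panel has no stated part in the exclusion decision. An analysis set defined elsewhere could keep an excluded patient in the analysis, but it could not supply measurements that were never taken.

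**Conclusion.** The concern holds in a limited form. The article states a rule under which an unblinded decision maker can end a randomised patient's follow-up because of an event related to the outcomes, and this rule does not agree with the section on discontinuing treatment. The two must be reconciled.

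The likely harm is missing later volumes, later revision status and 3-month mRS and NIHSS, possibly uneven between arms. Its size is unknown: it depends on how often SAEs occur and how often the PI excludes, and the article gives neither. The p-values and type I error rates for revision mark an assumed worst case, with recorded events deleted in one arm only, and should not be quoted as the expected effect.

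This should be fixed. It does not invalidate the design.

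**What to change.** Reword the sentence in {22} and align it with {11b}:

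- After an SAE the decision concerns only whether the allocated study treatment continues.
- The patient remains in scheduled follow-up to 3 months, unless he or she withdraws from participation, as {11b} allows at any time.
- Data collected up to that point are kept unless consent to data processing is withdrawn, as {27} already provides for withdrawal.
- The patient is analysed in the arm to which he or she was randomised.

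The clinical criteria for stopping treatment stay with the investigators and are not judged here.

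The cost is about one sentence and an amendment notice. Study visits already run parallel to routine outpatient follow-up {18b}, so no visits are added. Recruitment began in May 2024 (Trial status), and visits missed after an exclusion may not be recoverable, so the change is best made soon. Any patient already excluded after an SAE should be listed by arm, with the reason and the date.

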### Frequency and plans for auditing trial conduct {23}

The coordinating team will meet quarterly to discuss study progress, address any issues that may arise, and ensure compliance with the study protocol. The study steering committee, which includes the ethics committee of the leading study center, will meet quarterly. A data monitoring committee was not considered for this study because the intervention of this study is considered low risk.

### Plans for communicating important protocol amendments to relevant parties (e.g., trial participants, ethical committees) {25}

All relevant changes that may affect the conduct of the study, the study protocol or the safety of the participants are initially reported to the study sponsor. The change report to the participating centers is made via the PI, who sends the amended study protocol to the study officers at the respective centers, who add the updated protocol to the Investigator Site File. The amendment is reported to the ethics committees of the leading center and the participating centers in the form of a formal amendment application. In the case of changes that directly affect participants, the patient information sheets, and informed consent forms are adapted (which also will be added to the Investigator Site File) and all study participants are informed. Protocol amendments are updated in the German Clinical Trials Register as they occur. In general, any deviations from the trial protocol will be documented using a breach report form.

### Dissemination plans {31a}

Upon completion of the data collection, a comprehensive biometric report will be prepared by the principal investigator summarizing the key study findings and made available to the participating centers. Finally, the results will be discussed at a meeting of the participating researchers. In this context, a comprehensive publication and dissemination plan will be elaborated, including the publication of research results in the form of conference presentations and the publication of peer-reviewed research articles. In addition, a summary of the results and information on where they can be accessed will be published in the DRKS and thus made available to all interested parties.

## Discussion

We have described the protocol for a prospective, multicenter, randomized study comparing the influence of adjuvant drug therapy with tranexamic acid and additional endovascular embolization of the MMA after primary surgically relieved chronic subdural hematomas in terms of hematoma volume reduction, revision rate and safety of the procedures. The current study results indicate that both procedures can reduce the postoperative revision rate in particular. However, a randomized controlled trial is urgently needed to evaluate the risk–benefit ratio of additional embolization of the MMA compared to adjuvant drug therapy with TXA and, in this context, to identify patient entities with a comparable risk–benefit profile for whom one or the other adjuvant therapy is the appropriate treatment model. The prospective, multi-center design of this study promises a high level of evidence in this context.

